## Study Endpoints

### Primary efficacy endpoint:

- time until resolution of vasoplegic shock (defined as no need for vasopressors for at least 8 hours in order to sustain a MAD ≥ 65mmHg) in days

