### Secondary Endpoints:

- 7 day mortality after fulfilling the inclusion criteria
- mortality until hospital discharge
- measurement of IL-6 on day 1 and 3 of intervention
- need for mechanical ventilation
- duration of mechanical ventilation
- duration of ICU-stay
- catecholamine dose on day 1/2/3 after start of CytoSorb
- acute kidney injury

As primary endpoint we decided on the time until resolution of vasoplegic shock, a well implemented, clinically relevant endpoint in critical care. Two big intensive care studies already used this endpoint as secondary endpoint. (8, 9)

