# Study assessment

All laboratory determinations including will be analyzed locally.

Baseline variables:

- Age
- Sex
- Smoker status
- Comorbidities
  - Hypertension
  - Diabetes
  - Coronary heart disease
  - COPD
  - History of malignancy
  - Chronic kidney disease
  - Immunosuppression
  - Other

At inclusion

- Oxygen supplementation
- NIV/High Flow
- Intubation
- ECMO
- Vasoplegic shock
- Dose of Noradrenaline
- Other Vasopressors
- Glucocorticoids
- Antiviral treatment
- SOFA
- APACHE

Outcome parameters

- Time to resolution of shock (d)
- Need for mechanical ventilation
- Days on ventilator after inclusion (d)
- ICU survival
- In-hospital mortality
- 7 day mortality
- Septic shock
- Cardiogenic shock
- Acute kidney injury after Inclusion (AKIN-Stage 1,2,3)
- Dialysis
- Duration of ICU stay
- Vasopressor dose (max) on day 1
- Vasopressor dose (max) on day 2
- Vasopressor dose (max) on day 3
- Change to palliative therapy

Adverse events

- technical failure
- mashine clotting
- other

Serious adverse events

- Cardiac arrest
- Severe bleeding
- Severe allergic reaction
- Severe Complication due to shaldon catheter insertion
- Death
- Other

Complication possibly associated with CytoSorb

- Heparin induced thrombycytopenia Type 2 (HIT 2) if heparine is exclusively needed for CytoSorb therapy
- Complication associated with shaldon catheter insertion if catheter is exclusively needed for CytoSorb therapy
- Severe allergic reaction associated with CytoSorb therapy
- Other

Laboratory Data (day 1+3+7)

- CRP
- Troponin
- D-Dimer
- IL-6 (Only Day 1+3)
- Ferritin
- LDH
- Creatinine
- ALT
- PCT
- Phosphate

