# Statistical analysis

A recent retrospective observational study showed a mortality of 61.5% in a cohort of 52 critically ill COVID-19 patients. (18) Due to both the explorative character of the study (new virus, heterogeneous data on efficacy of CytoSorb-treatment in general an no data in COVID-19-patients at all) and few data on possible recruiting rates (patient flow not estimable, patient condition not estimable) we cannot make assumptions on the effect size of the intervention. That is why, supported by the Institute of Biometry and Clinical Epidemiology of the Charité, we decided on an investigator-initiated clinical pilotstudy in order to evaluate the feasibility of recruitment and gain knowledge concerning the intervention effect. We will consecutively include all eligible patients for a period of eight weeks and randomize them to either receive CytoSorb treatment or standard of care without CytoSorb in order to plan an adequately powered randomized controlled trial with the gained knowledge on effect size and recruitment feasibility as a subsequent trial.

The primary analysis in order to evaluate the effect of the intervention will be carried out with a shared frailty model with time until resolution of vasoplegic shock as outcome variable censored at the time of death. The randomization group will be included as fixed effect and additionally possible confounder such as age, sex and pre-existing illness.

The intensive care unit where the patient is treated will be added as random effect in the model in order to control for cluster effects.

As an additional analysis, death will be treated as competing risk, results will be shown in a cumulative incidence function.

Secondary endpoints will be evaluated with adequate models (proportional hazards model / ANCOVA / logistic regression) depending on distribution of endpoint variables.

All the analyses will be explorative and will not be controlled for multiple testing. Since missing data is not expected, imputation is not planned.

Blinding of the investigator and patient is not possible as a clinical intervention is done, statistician will receive a blinded data set, so that all analyses will be conducted blinded.

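### The day 2 and day 3 catecholamine doses have no rule for patients whose vasopressors were withdrawn for palliation, so withdrawal of support can read as improvement.

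*Protocol*

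**What the plan says.** Under Study assessment, the outcome parameters include "Change to palliative therapy". The item appears nowhere else in the protocol.

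The secondary endpoints include "catecholamine dose on day 1/2/3 after start of CytoSorb". The matching data items under Study assessment are daily maxima, for example "Vasopressor dose (max) on day 2", with the same form for days 1 and 3. Neither place attaches a condition to the value. For secondary endpoints, the Statistical analysis section says only that the model will be chosen to suit the distribution. It adds that missing data are not expected.

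The primary endpoint is time to resolution of vasoplegic shock, where resolution means "no need for vasopressors for at least 8 hours in order to sustain a MAD ≥ 65mmHg". The primary model takes "time until resolution of vasoplegic shock as outcome variable censored at the time of death". A further analysis is announced: "As an additional analysis, death will be treated as competing risk". No other terminal event is named.

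Treatment is open-label (Intervention scheme; Blinding assessment), and the statistician works on a blinded data set.

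**The concern.** By listing a change to palliative therapy among a deliberately short set of outcome variables, the protocol signals that it expects such changes. If vasopressors are then stopped, the reason is that the pressure goal has been given up, not that shock has improved. The recorded dose cannot tell these two reasons apart.

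This differs from a value lost to death. Here the patient is alive, a value exists, and the value misleads. Neither censoring at death nor missing-data handling removes it.

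Two features make it worth settling. Clinicians know the arm, so the frequency or timing of palliative decisions could differ between arms, although nothing in the protocol says that it will. And the stated purpose of the pilot is to learn the effect size for a later powered trial, so a dose difference produced by withdrawal of support could carry into that planning.

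**Working it through.** There is no planned figure to reproduce. The 85 to 100 patients are a recruitment expectation, and the point does not depend on that number. The check is a reading of the definitions, followed by an illustration.

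**1. Dose endpoint, followed as written.** Take a patient on vasopressors on day 1 whose care becomes palliative during day 2, with vasopressors stopped then, and who is still alive on day 3.

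| Day | Recorded daily maximum | Meaning |
|---|---|---|
| 1 | dose under full support | valid |
| 2 | normally the peak before withdrawal | valid |
| 3 | zero or low | support withdrawn, read as improvement |

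Because the daily maximum is recorded, the distortion begins on the day after the change. It therefore falls mainly on days 2 and 3 and hardly on day 1.

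**2. Illustration of size.** Let w be the share of living patients in an arm whose dose is zero after withdrawal, and mu the mean dose in the others.

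- Arm mean = mu × (1 − w), so the fall is mu × w.
- Assumed inputs: w = 5% to 20%; mu = 0.2 to 0.4 µg/kg/min. The lower value of mu equals the noradrenaline entry threshold in the inclusion criteria and the upper value is twice that. The protocol gives neither w nor mu.
- Smallest: 0.2 × 0.05 = 0.01 µg/kg/min. Largest: 0.4 × 0.20 = 0.08 µg/kg/min. In relative terms the fall equals w, that is 5% to 20%.
- With the same mu in both arms, the spurious difference between arms is mu × (w₁ − w₀). It is zero if the shares are equal. With 20% against 5% it is 0.2 × 0.15 = 0.03 to 0.4 × 0.15 = 0.06 µg/kg/min, in favour of the arm with more withdrawal.

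**3. Primary endpoint, followed as written.** Being off vasopressors is not enough. They must not be needed to hold the pressure target, for at least 8 hours.

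- Support withdrawn and pressure falls below target: not resolved.
- Death within 8 hours of withdrawal: the window cannot be completed, and the patient is censored at death.
- Pressure holds at or above target for 8 hours without vasopressors: the definition is met.

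A false event therefore requires an entry that goes against the definition.

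**4. What could reveal such an entry?** The outcome item is a time in days. No blood-pressure variable is listed under Study assessment, so the listed data cannot confirm the pressure condition. A blinded statistician could not recognise a wrong entry from that number alone.

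**5. Status of a palliated, living, unresolved patient.** Only death is named as a censoring or competing event. The protocol does not say whether such a patient stays at risk, is censored, or has a competing event.

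**The case against.** A reader might infer that withdrawal of support will be counted as shock resolution and will inflate the primary events in the arm with more palliation. The documents do not support this. The definition ties resolution to the need for vasopressors to sustain a pressure target, which excludes the case when read literally. Any percentage for inflated events would presuppose miscoding, at a rate found nowhere in the protocol. It would also need a resolution rate, and the 61.5% mortality cited under Statistical analysis does not supply one: it comes from an external cohort of 52 patients, and a patient can resolve shock and die later.

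A second objection is that rules for such events are commonly left to the statistical analysis plan, which the Data Sharing Statement mentions and which is not at hand. This has force for the choice of ranking rule and sensitivity analysis, which may be settled there. It has less force for the endpoint definition and the list of data to be collected, which the protocol itself sets. If the timing of the change is not captured, no later plan can separate doses before it from doses after it. The list of variables is not the layout of the case report form, however, so a date may already be recorded.

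Third, the protocol does not say what a palliative change entails, how often it occurs, or that it will differ by arm. That stands, and it is why no size can be claimed. Finally, the dose is one of eight secondary endpoints in a pilot whose analyses are all declared explorative. That limits the severity but does not remove the point, because a sentence and a time stamp would settle it.

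**Conclusion.** The point holds for the dose endpoint. Under the protocol's wording, a patient alive after withdrawal of vasopressors gives a low or zero maximum on later days, and no stated rule keeps it from counting as a good result. The effect falls on days 2 and 3.

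For the primary endpoint the point is narrower. The definition is sound on a literal reading. What remains is a judgement of need by unblinded staff that the listed data cannot verify, and an unstated status for palliated patients who are alive and unresolved.

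The protocol gives no basis for sizing either effect. The fall of 0.01 to 0.08 µg/kg/min in an arm's mean dose is an illustration on assumed rates. A bias between arms arises only if the arms differ in withdrawal or in underlying dose. Severity is minor to moderate.

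**What to change.** These changes concern recording and analysis only.

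- Make sure that the date and time of the change to palliative therapy are captured.
- For the day 2 and day 3 comparisons, do not analyse doses from the day after the change as observed low values. One option is to give them the worst rank in a rank-based analysis. Leave the maximum on the day of the change as recorded, since it normally reflects full support. State alongside this how patients who have died before that day enter the comparison.
- Add one sentence to the primary endpoint: cessation of vasopressors at or after the change to palliative therapy does not count as resolution of shock.
- Keep the planned analyses, and add a sensitivity cumulative-incidence analysis with palliative change or death as a single competing event.
- Report palliative changes, with their timing, by arm.

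The cost is at most one time stamp on a variable already listed, a few sentences, and one extra analysis. Worst-rank scoring is one choice among several and does not fit an ANCOVA on the raw dose, so the dose analysis would have to be rank-based. The small downside is that a few patients' values are then set by a treatment-limitation decision rather than by a measurement.

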### Exclusion criteria:

- Patients receiving Tocilizumab (anti-IL6-receptor antibody)
- Patients not applicable for anticoagulation (if Heparin is not applicable local anticoagulation with citrate or systemic Argatroban can be used, severe thrombocytopenia < 20.000/μl is a contraindication
- pregnancy
- bacterial infection

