# Safety assurance

## Safety of the procedure

Apart from the invasiveness of the procedure (there is the need for a big central venous access that most critical patients need anyway) the method is known to be safe. (12, 13) (15) Possible complications associated with the implementation of the central venous access are bleeding, infection, malpuncture including arterial malpuncture, damage to surrounding organs including lung injuries requiring drainage, thromboses, embolisms and in very rare cases strokes. Rarely allergic reactions to the system are described, (17) which would lead to immediate disruption of the therapy and adequate antiallergic therapy. There is the need for anticoagulation (PTT aim 60-80), which is usually done with Heparine. Heparin induced thrombocytopenia (HIT) is a known adverse events associated with heparin. In suspected or proven HIT patients heparin will be stopped immediately. Alternative anticoagulation (citrate or Argatroban) can be used. For patients with increased risk of bleeding citrate anticoagulation is possible. Since it cannot be excluded that drugs, including antibiotics, are partially removed by the filter, patients receiving antibiotic therapy receive an additional antibiotic dosage after each filter change to avoid underdosage.

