## Safety assessment

CytoSorb is a medical device which is already well implemented in routine clinical practice and CE-certified in the European Union. Several clinical studies and also a large registry have not shown any serious side effects. It can be assumed that this can also be transferred to the study participants. The medical device is used within the scope of its approval.

However, in order to exclude risks for the study participants a safety surveillance system will be established and will follow the applicable legislation, standards and SOPs of the CSC Charité. Treating physician visits all patients at least twice a day and any adverse event is documented in the patient file as well as in the eCRF of the electronic database and assessed by the investigators for seriousness. SAE will be sent within 24 hours to the sponsor/medical monitor of the trial. A data safety monitoring board (DSMB) with three external reviewers will review the safety during the trial. It is proposed that the DSMB will meet at regular intervals (after every 10 patients included in each randomization group) via videoconference after start of the trial, to review the safety data of the study. Moreover, members of the DMSB will be informed about adverse events every 2 weeks in between the meetings or immediately in case of the occurrence of unexpected events. In addition, members of the DMSB will be informed on the progress of the trial (in particular recruitment and dropout rate) and will give written recommendations to the funding organization if the study should be discontinued. After the inclusion of 10 patients in each randomization group a report is given to the local ethics committee of the Charité.

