## Criteria for Study discontinuation

Stopping rules for the individual patient is patient wish, adverse event (e.g. allergic reaction to CytoSorb, contraindication for anticoagulation, severe thrombocytopenia (<20000/ /μl) or proven bacterial infection during treatment course as we want to see the effect of CytoSorb on suspected cytokine storm and distinguish from other effects leading to vasoplegic shock such as sepsis.

As CytoSorb is already part of routine clinical practice and well known to the users and because of the short trial duration of 8 weeks we did not put restrictions on inclusion rates for each participating site.

Stopping rules for the whole trial are safety concerns due to the ongoing surveillance of mortality and adverse events by investigators as well as the DSMB. Furthermore, an interim analysis of the data is done after the inclusion of 10 patients in each group and a new consultation of the ethics committee is mandatory.

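### The listed follow-up data hold no platelet count, PTT, haemoglobin or anticoagulant type, and HIT is recorded only on the CytoSorb side, so the platelet stopping threshold and these harms are visible by arm only through unscheduled event reports

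*Protocol*

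**What the plan says.** **The risk and the rules built on it.** Safety of the procedure states: "There is the need for anticoagulation (PTT aim 60-80), which is usually done with Heparine". It names HIT as a known adverse event of heparin and allows a switch: "Alternative anticoagulation (citrate or Argatroban) can be used". The Exclusion criteria bar patients with "severe thrombocytopenia < 20.000" per µl. Criteria for Study discontinuation uses the same threshold to stop treatment in the individual patient, listing "contraindication for anticoagulation, severe thrombocytopenia" among its reasons.

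**The data to be collected.** Study assessment heads its laboratory list "Laboratory Data (day 1+3+7") and names CRP, troponin, D-dimer, IL-6 (days 1 and 3 only), ferritin, LDH, creatinine, ALT, PCT and phosphate. The adverse events are technical failure, machine clotting and 'other'. The serious adverse events include "Severe bleeding" and 'other'. Under complications possibly associated with CytoSorb, the HIT item reads "Heparin induced thrombycytopenia Type 2 (HIT 2) if heparine is exclusively needed for CytoSorb therapy".

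**Event reporting.** Safety assessment says that "any adverse event is documented in the patient file as well as in the eCRF of the electronic database". SAEs go to the sponsor within 24 hours, and the DSMB hears of adverse events every two weeks, or at once if they are unexpected.

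**The concern.** The protocol relies on a PTT target, a platelet threshold and a HIT risk, but its own list of follow-up variables contains none of the measurements behind them. A site can apply the stopping rule from the patient's chart. The trial data set, as listed, holds no scheduled value that shows whether the threshold was crossed, whether platelets fell more in one arm, or whether bleeding went with a particular anticoagulant or PTT level.

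The trial is open-label, and staff caring for device patients have a platelet stopping rule in mind. If low platelets reach the database only when someone chooses to report them, ascertainment may differ between arms. The HIT item is unequal by construction, because its condition can be met only by patients on CytoSorb.

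The pilot is meant to inform a larger trial. Without these data it would end with little comparable information on the haematological side of a device that requires anticoagulation.

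**Working it through.** There is no plan figure to reproduce. The check compares each safety provision with the items in Study assessment.

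| Provision in the protocol | Matching follow-up item | Result |
|---|---|---|
| PTT aim 60–80 (Safety of the procedure) | PTT | Absent |
| Heparin, citrate or argatroban (Safety of the procedure; Exclusion criteria) | Anticoagulant type | Absent |
| Platelets below 20,000/µl as exclusion and stopping rule | Platelet count | Absent; SOFA is listed at inclusion only, so any platelet information in it is baseline |
| The same threshold as an event | Thrombocytopenia item | None of its own; only 'other' AE or SAE |
| HIT as a known adverse event | HIT type 2 | Present, but only if heparin is needed solely for CytoSorb |
| Bleeding | Severe bleeding as SAE | Present, no arm restriction |
| Bleeding, laboratory side | Haemoglobin | Absent |

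**The HIT condition.** Control patients never receive CytoSorb, so none can satisfy it. CytoSorb patients who need heparin for another reason as well also fall outside it. The item thus has no comparator and may be incomplete even in the device arm.

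**Patients concerned.** The protocol expects 85–100 patients and states no allocation ratio. Assuming 1:1, the device arm has 85/2 = 42.5 to 100/2 = 50 patients, that is about 42–50. Not all of them are newly exposed to heparin: the wording of the HIT item implies that some receive it for other reasons, and citrate or argatroban may be used instead.

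**Data burden.**
- Current schedule: nine analytes × 3 days + IL-6 × 2 days = 27 + 2 = 29 values per patient.
- Adding platelets, PTT and haemoglobin on days 1, 3 and 7: 3 × 3 = 9 values, giving 38; 9/29 ≈ 31% more.
- For comparison, the same three daily on days 1 to 8: 3 × 8 = 24 values; 24/29 ≈ 83% more.

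The first option fits the existing visit days. The second would nearly double the laboratory entries.

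**The case against.** **A reader might infer that the trial and the DSMB cannot assess these harms between arms at all.** The protocol does not support that. Severe bleeding is an SAE item in both arms. Criteria for Study discontinuation can be read as naming severe thrombocytopenia as an example of an adverse event, and Safety assessment sends every adverse event to the eCRF without arm restriction. On that reading, reaching the threshold is reportable in either arm through 'other'. This stands, and it limits the point to the missing scheduled values, the missing exposure field and the unequal HIT item.

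**A reader might also infer that day 7 is too early a last sample** because treatment can start up to 24 hours after eligibility and last 7 days. That depends on where day 1 is anchored. The endpoint lists count IL-6 days from the intervention and catecholamine days from the start of CytoSorb. On that count, day 7 is the last possible treatment day. Sampling to day 8 is therefore not needed on this argument.

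**The eCRF is lean on purpose.** Data management says that collection is confined to the most important outcomes because of the acute situation. That is a fair reason for brevity. It does not explain the selection: phosphate, ferritin, LDH and troponin are listed although no stated endpoint or stopping rule rests on them, while the marker for a stated exclusion and stopping rule is left out.

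**The SAP or the actual eCRF may hold more.** Neither is shown. A SAP analyses what is collected, whereas the protocol sets what must be collected. Data management ties the eCRF to protocol-required information, and Study assessment is the list of it. An eCRF with more fields would lessen the gap, but this document does not require one.

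**Conclusion.** The point holds in a limited form. None of the ten follow-up analytes is platelets, PTT or haemoglobin, and no item records the anticoagulant. From the listed data, the laboratory course and anticoagulant exposure cannot be compared by arm. Use of the platelet stopping threshold can be seen only through unscheduled reports in an open-label trial, and HIT type 2 has no control-arm counterpart. Severe bleeding can be compared, and adverse events do reach the eCRF and the DSMB.

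About 42–50 device patients are concerned, assuming 1:1 allocation. No bias in any result can be quantified from the document. The conclusion assumes that Study assessment is the full list of required data. This is an inexpensive improvement to what the pilot can say about safety, not a flaw in the primary analysis.

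**What to change.** In Study assessment, for both arms:

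- Add platelets, PTT and haemoglobin, taken from routine ICU results, to the existing day 1, 3 and 7 laboratory data.
- Record the type of anticoagulation (heparin, citrate, argatroban or none).
- List platelets below 20,000/µl (the protocol's own threshold) and HIT as events, and put attribution to CytoSorb in a separate field instead of making it a condition for recording HIT.
- Tabulate these events and severe bleeding by arm for the DSMB.

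No clinical rule changes, and because the values come from routine results, no new samples are planned. The cost is nine more laboratory values per patient (29 to 38), one or two more fields for anticoagulant and attribution, and the two event entries. The downside is somewhat more data entry in an eCRF that was kept short on purpose.
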